### Sample size

To calculate the sample size required, the non-inferiority margin (i.e., tolerable amount of effect difference between TAU and the UP) has to be set. This was done according to the US Food and Drug Administration (FAD) [16] guidelines. First, the effect of the active control (i.e., CBT) compared with placebo needs to be established, based on previous research. Meta-analyses indicate medium-to-large effect sizes (between .4 and .8) of individual CBT on EDs [17–19]. Then, an amount of minimum preserved effect needs to be set. According to FDA guidelines, a preserved effect of a 50% of the effect of the active control (individual CBT) is recommended, so this was set to .3 in the present study. Because, to the best of our knowledge, no meta-analysis has reported effect sizes for each outcome included in the study, the margin has been defined according to the pooled estimate of overall effectiveness of CBT.

With regards to treatment satisfaction, a 35% non-inferiority margin was established. This is based on a meta-analysis of computer CBT, in which between 70% and 100% of depressed patients were satisfied with treatment [20]. To the best of our knowledge, there is no meta-analysis of treatment satisfaction with individual, face-to-face CBT and its study is rare. However, similar to group UP, computer CBT has been argued to be an alternative to traditional CBT [20], especially when resources are limited, so the aforementioned satisfaction rates of computer CBT might be relevant in the present study.

We obtained a sample size of 95 participants for each group with 80% power, an alpha level of .05 (one-sided), a standard deviation of .83 in the CBT group compared with placebo, and a non-inferiority limit of .30 [21, 22]. Considering a drop-out of 15%, we decided to recruit 110 subjects in each group. When registering the study, a sample size of 200 individuals was calculated. However, this was increased by 20 patients after considering non-inferiority sample size calculations.

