### Procedure

Randomization has been performed by a researcher unrelated to the study using a computer-generated sequence (Randomizer). In the program, the researcher generated 1 set of numbers with 220 numbers, which had a 1-to-2 range. Randomization is stratified according to the severity of the primary measures of depression (BDI-II) [23, 24] and anxiety (BAI) [25, 26], using the recommended cut-off in manuals. In the BDI-II, these are 0–13 for normal, 14–19 for mild, 20–28 for moderate, and for 29–63: severe depressive symptoms [24]. As for anxiety symptoms (BAI), cut-off are 0–7 for normal, 10–18 for mild, 16–25 for moderate, and 26–63 for severe [26]. Stratification is made to ensure a comparable proportion of severely depressed and anxious individuals in each group. For each subgroup (i.e., severe or less severe depression and/or anxiety), participants are randomly assigned to the UP or to TAU. In the UP condition, there are between 8 and 10 participants and 2 clinicians (therapist and co-therapist) per group. In the TAU condition, participants receive individual sessions with one therapist.

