### Analyses

First, we will calculate between-group differences in baseline measures, to ensure that randomization resulted in comparable groups. When normally distributed, continuous data will be analyzed via *t* test. If the Kolmogorov-Smirnov test indicates a non-normal distribution, a Mann-Whitney *U* test will be preferred. A chi-square test will be performed for categorical data. Then, to compare the efficacy of treatments, we will use a mixed-effects regression modeling with full information maximum likely hood estimation. This method is recommended over repeated-measures ANOVAs due to its flexibility in handling missing data [39]. Group (TAU or UP) will be used as the between-subject factor and time (baseline, post-treatment, and follow-ups) as the within-subject factor. Standardized effect sizes (Cohen’s *d*) will be calculated both for within and between-group analyses. Covariates will be demographic and clinical variables that are not comparable between groups, as exposed in the beginning of this section. Effect estimators in the UP group will be adjusted to control for the impact of group dependencies (i.e., homogenization of response to treatment due to shared environment), following the recommendations of Baldwin et al. [40].

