To address problems of missing data or premature dropouts, an intention-to-treat analysis will be used and the most recent data will be imputed (last observation carried forward approach). This analytic strategy will only be performed with patients attending at least 50% of sessions, as recommended in past research [41], and with those responding to at least one of the post-treatment assessments (i.e., end of treatment or follow-ups) so that treatment effect may be captured by the last observation. In addition to the last observation forward, missing data in the UP group will also be replaced with the CBT mean +/− the non-inferiority margin and missing data in the CBT group will be replaced with the UP mean (i.e., bias toward inferiority) [42]. Results using a last observation carried forward approach and a bias toward inferiority imputation will be compared against a completers-only strategy and all of them will be reported. To ensure non-inferiority, a per-protocol analysis will also be conducted. Following FDA guidelines [16], non-inferiority will be concluded if the upper bound of the 95% CI for the effect estimate in the UP condition is smaller than the non-inferiority margin (50% of the effect estimate of individual CBT when compared to placebo). Due to the non-inferiority design (i.e., the Unified Protocol in a group format is not worse than individual CBT), a one-sided confidence interval will be used in the analyses. A post-hoc power analysis with the primary outcomes will be conducted at post-treatment and follow-ups using the sample size and obtained effect size.

The researcher analyzing data, [name], will be blind to arm allocation. To ensure that, arms will be given arbitrary letters (A and B) in the database and only the lead researcher, [name], will know the correspondence between study allocation arms and assigned arbitrary letters.

Reporting of results will follow the Consolidated Standards of Reporting Trials (CONSORT) recommendations [43].

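### The stated 80% power is not supported: a standardised margin of .30 is paired with an unexplained SD of .83, and the UP therapy groups get no allowance

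*Protocol article*

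**What the plan says.** All references are to the protocol article.

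- **Sample size, margin.** The starting point is a range of standardised effects: "Meta-analyses indicate medium-to-large effect sizes (between .4 and .8) of individual CBT on EDs". Half of the control effect is to be preserved, and the margin is set at .3, which is half of the midpoint .6. The section says that the margin rests on a pooled estimate of CBT effectiveness because no outcome-specific estimates were found. It is therefore tied to no questionnaire's raw scale.
- **Sample size, calculation.** "We obtained a sample size of 95 participants for each group with 80% power", with one-sided alpha .05, "a standard deviation of .83 in the CBT group compared with placebo, and a non-inferiority limit of .30". The only inflation is 15% for drop-out, giving 110 per arm.
- **Procedure.** In the UP arm "there are between 8 and 10 participants and 2 clinicians (therapist and co-therapist) per group". TAU is delivered individually. The Discussion gives a different UP group size, 6 to 8.
- **Analyses.** Between-group effects will be reported as Cohen's d, and "Effect estimators in the UP group will be adjusted to control for the impact of group dependencies". The decision rule compares the confidence bound with half of the CBT-versus-placebo effect, and "a one-sided confidence interval will be used in the analyses".

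**The concern.** Two inputs do not fit the rest of the plan.

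1. **Scale.** A margin derived by halving a standardised effect is already in SD units. On that scale the between-patient SD of an unadjusted outcome is 1. An SD of .83 belongs either to some other scale, which the article does not name, or to a residual after covariate adjustment, which the article does not claim.
2. **Clustering.** The analysis will allow for similarity among patients treated in the same UP group. The sample size treats all patients as independent.

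Both choices make the stated power higher than it would otherwise be. A reader of an inconclusive result would assume a 20% risk of missing non-inferiority between equal treatments, when that risk could be considerably larger. The mismatch also leaves it unclear whether the tolerated loss is 0.30 or 0.36 SD.

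**Working it through.** **Inputs from the article:** margin 0.30; SD 0.83; one-sided alpha 0.05 (z = 1.645); power 80% (z = 0.842); 95 evaluable per arm; 8 to 10 patients per UP group (6 to 8 in the Discussion). **Assumed:** true difference 0, the value that reproduces the stated n; ICC 0 to 0.10, because the article gives none; 9 patients per group, with 7 as a check.

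**Step 1. Reproduce the plan's figure.** n per arm = 2 × (1.645 + 0.842)² × SD² / margin² = 2 × 6.183 × 0.6889 / 0.09 = 94.6, so 95. This matches. The arithmetic is right, and it leaves no room for a design effect.

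**Step 2. What margin was sized for?** 0.30 / 0.83 = 0.36 SD, which is 20% wider than the 0.30 that was derived.

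**Step 3. Same formula with SD 1.** n = 2 × 6.183 × 1 / 0.09 = 137.4, so 138 per arm. Power at 95 per arm = Φ(0.30 / √(2/95) − 1.645) = Φ(2.068 − 1.645) = Φ(0.423) = 66.4%.

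**Step 4. Add clustering in the UP arm only.** Design effect DE = 1 + (m − 1) × ICC, and power = Φ(0.30 / (SD × √((DE + 1)/95)) − 1.645). For example, with SD 1, m = 9 and ICC 0.05: DE = 1.40, standard error = √(2.40/95) = 0.159, power = Φ(1.887 − 1.645) = 59.6%.

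| ICC (assumed), m = 9 | DE | Power, SD 1 | Power, SD 0.83 |
|---|---|---|---|
| 0 | 1.00 | 66.4% | 80.1% |
| 0.02 | 1.16 | 63.5% | 77.4% |
| 0.05 | 1.40 | 59.6% | 73.5% |
| 0.10 | 1.80 | 54.1% | 67.7% |

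With m = 7 and ICC 0.05 (DE = 1.30), power is 61.1% with SD 1 and 75.1% with SD 0.83. The difference between the two stated group sizes therefore matters little.

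**Step 5. When would 0.83 be right?** A baseline-adjusted outcome has residual SD √(1 − r²), where r is the baseline-outcome correlation. For r = 0.56 this is √(1 − 0.3136) = 0.83. Without clustering, power at 95 per arm is 73% at r = 0.4, 77% at r = 0.5 and 80% at r = 0.56. If the contrast were simple change from baseline, r = 0.5 gives SD √(2 × 0.5) = 1 and 66% again.

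**The case against.** The strongest reply is that 66% is not the power of the planned analysis either. The Analyses section specifies a mixed-effects model with baseline and follow-ups in the time factor, and randomisation is stratified on baseline severity. If the treatment contrast is in effect baseline-adjusted, the relevant SD is below 1 and .83 is attainable. The clustering figures rest on an ICC that the article does not give: at 0.02 with SD .83 the loss is under 3 points. The article also plans to adjust for group dependency, so the inference itself is protected. Using 9 per group with 95 patients after drop-out is slightly pessimistic, since the same 15% loss would leave about 9 × 0.85 = 7.65 per group.

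Most of this stands, and it limits the conclusion. A reader might go further in four ways that the document does not support.

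- *That the trial's power is simply 60% to 66%.* That range assumes an unadjusted single endpoint and, at its lower end, a chosen ICC. The article fixes neither the contrast nor a baseline-outcome correlation.
- *That equal treatments would probably fail.* Even at 54% power, success is more likely than failure.
- *That a false claim of non-inferiority becomes more likely.* Lower power does not raise that risk, and the one-sided .05 level agrees between the Sample size and Analyses sections.
- *That the drop-out line is a material error.* 110 × 0.85 = 93.5 evaluable instead of 95, which gives 79.6% power, a loss of about half a point.

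The reply does not rescue the stated 80%. The article describes .83 as an SD in the CBT group relative to placebo, not as a residual SD. Even on the residual reading, the UP design effect is still missing.

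**Conclusion.** The point holds as a mismatch of inputs, not an error of calculation. The 80% figure is obtained only with SD .83 and independent patients. The first is unexplained on the margin's own scale, and the second conflicts with the planned analysis.

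On an unadjusted comparison, power is about 66% without clustering and falls to about 54% at ICC 0.10. If .83 is a residual SD, it is 80% without clustering and falls to about 68%. For ICCs of 0 to 0.05 in the unadjusted case, the chance of missing non-inferiority between equal treatments is about 34% to 40% on a given outcome, against 20% implied.

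The SD 1 result without clustering uses the article's own inputs, the scale of its margin and a true difference of 0. The clustered figures rest on assumed ICCs and group size. Where .83 came from cannot be settled from the article, so it is unexplained rather than shown to be wrong.

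**What to change.** Keep 220 patients and revise the Sample size section as follows.

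1. State one scale for the margin and the SD. If the margin is 0.30 in SD units, use SD 1 for an unadjusted comparison.
2. Restate power as a range, with the UP design effect, the assumed ICCs and the group size declared. The table above can serve. Reconcile the two UP group sizes given in Procedure and Discussion.
3. Keep .83 only if it is justified as a residual SD after baseline adjustment (correlation about 0.56) and the baseline-adjusted model is named as primary. The UP design effect is still needed.

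The cost is a less favourable stated power. No patients are added, and the margin and decision rule stay as they are.

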### Sample and recruitment

The trial started the recruitment in September 2014 and it is still active. The study is conducted in five different Public Mental Health Centers and Primary Care Centers in Spain, namely, the Elda Clinical General Hospital, the Hospital Clínico Universitario de Valencia, the [name] Hospital, the PCC IIA Milagrosa of Pamplona, and the Hospital Comarcal de Vinaròs. Participants are individuals over 18 years of age seeking psychological assistance in the Spanish Public Health System. Sample size was set to 220 participants to ensure enough statistical power when testing our hypotheses (see “Sample size” section).

Patients are referred to the study by licensed psychologists, psychiatrists, and clinical psychology residents working at the collaborating centers, who also assess for current DSM diagnoses (See “measures” section) and the remaining eligibility criteria (see “Inclusion and exclusion criteria” section). Individuals with comorbid diagnosis of several EDs are also enrolled in the study. The existence of such comorbidities might be important for assessment scores. However, in the present study we did not stratify considering comorbidities because this could significantly increase the complexity of the design (i.e., some patients might have more than one comorbid diagnosis). Due to the difficulties derived from conducting an RCT in different public mental health settings, we cannot guarantee a 100% of independent evaluations. We expect between 60 to 75% of independent evaluations. The rest of evaluations will probably be made by recruiters who are also the therapists in one of the conditions. However, this information is collected and considered in the interpretation of results.

Patients meeting eligibility criteria are asked to participate and are provided with an information sheet, information on data confidentiality, and an informed consent form. After participation acceptance, patients complete the baseline assessment protocol in their correspondent health center (see “Measures” section). Next, participants are informed of the condition they have been randomly assigned to, that is, TAU or UP.

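### The 15% drop-out allowance and the figures of 95 and 110 per arm do not quite fit together: 110 per arm covers about 13.6% drop-out, with a negligible effect on power

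*Protocol article*

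**What the plan says.** The Sample size section of the protocol article gives the base requirement: "We obtained a sample size of 95 participants for each group with 80% power". The inputs are "an alpha level of .05 (one-sided"), "a standard deviation of .83 in the CBT group compared with placebo", and "a non-inferiority limit of .30". The next sentence moves from this requirement to the recruitment target: "Considering a drop-out of 15%, we decided to recruit 110 subjects in each group".

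The Sample and recruitment section relies on the resulting total: "Sample size was set to 220 participants to ensure enough statistical power when testing our hypotheses". The Sample size section adds that 200 patients were planned at registration and that 20 were added once the non-inferiority calculation had been considered.

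The article does not show how 95 became 110, and it does not state how many patients are expected to remain after drop-out.

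**The concern.** An allowance for drop-out is meant to leave the required number of patients once the expected share has been lost. If 15% of the recruited patients drop out, the recruitment target has to be the required number divided by 0.85. Multiplying the required number by 1.15 treats drop-out as a share of those who stay and gives too small a target.

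The stated 110 is what the multiplication gives after rounding up. By either route, 110 less 15% is below 95, so the three figures (95 required, 15% lost, 110 recruited) cannot all hold. The base figure offers little cushion, because 95 is the smallest whole number that meets 80% on the stated inputs.

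What is at stake is the accuracy of a stated planning figure. Readers will compare the observed attrition with the 15% and take anything up to that level as fully provided for.

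**Working it through.** **Inputs, all from the Sample size section of the protocol article unless marked**

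- Margin .30; SD .83; one-sided alpha .05; power 80%
- Required number per arm: 95
- Drop-out 15%; recruitment 110 per arm, 220 in total
- True difference between arms: 0 (assumption; the article does not state it, but it reproduces the 95)
- Every drop-out contributes nothing to the analysis (assumption)

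**Step 1. Reproduce the plan's base figure**

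n per arm = 2 × (SD / margin)² × (z₀.₉₅ + z₀.₈₀)²
= 2 × (.83 / .30)² × (1.645 + 0.842)²
= 94.65, rounded up to 95.

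This matches the stated 95 exactly.

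**Step 2. Inflate for 15% drop-out**

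- Division: 95 / (1 − 0.15) = 111.8, rounded up to 112 per arm, 224 in total.
- Multiplication: 95 × 1.15 = 109.25, rounded up to 110 per arm, 220 in total.

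The stated target equals the second result. It is 2 per arm (4 in total) below the first.

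**Step 3. Patients left under the stated figures**

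- Per arm: 110 × 0.85 = 93.5, against 95.
- In total: 220 × 0.85 = 187, against 2 × 95 = 190. The shortfall in evaluable patients is 3.

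**Step 4. Drop-out that 110 per arm covers**

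1 − 95/110 = 13.6%.

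**Step 5. Power on the plan's inputs**

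Power = Φ( .30 / (.83 × √(2/n)) − 1.645 )

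| Evaluable per arm | Total | Power |
|---|---|---|
| 95 | 190 | 80.1% |
| 93.5 | 187 | 79.6% |

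The loss is about 0.5 percentage points against 95 per arm, and about 0.4 points against the stated 80%.

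The comparison has to stay within one method. With the noncentral t distribution, 95 per arm already gives 79.9% and 93 gives 79.1%. Setting the t figure for 93 beside the normal figure for 95 would overstate the loss.

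**The case against.** **The mechanism is not documented.** The article shows no inflation formula. A target of 110 could also be 111.8 taken to a round number, and 220 is also the registered 200 plus 20. This objection stands as far as it goes: a reader might infer that the authors multiplied by 1.15, and the match supports that, but the text does not establish it. The inconsistency does not depend on the mechanism, since 110 less 15% is below 95 however the 110 was reached.

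**Drop-outs are not all lost.** The Analyses section plans a mixed-effects model with full-information maximum likelihood, last observation carried forward, and an imputation biased toward inferiority. A patient who misses a later follow-up can still contribute. This stands in part. An allowance for drop-out by its nature treats drop-outs as lost, so the allowance has to be judged on that premise. The carried-forward analysis is also restricted: "This analytic strategy will only be performed with patients attending at least 50% of sessions", and only with at least one post-treatment assessment. The completers-only and per-protocol analyses may lose drop-outs outright. The shortfall therefore depends on the analysis set, and the figures above are the case in which every drop-out is lost.

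**It is immaterial.** Power of 79.6% rounds to the stated 80%. The precision of the SD matters more than this shortfall: .825 and .835 both lie within rounding of .83, and the required number is then 94.65 × (.825/.83)² = 93.5 or 94.65 × (.835/.83)² = 95.8 per arm. This stands, and it sets the severity.

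**A stronger reading is tempting.** A reader might infer that the trial is underpowered because of this slip, or that it must enrol 4 more patients. The document's own figures do not support either: the loss is under half a percentage point against the stated 80%, and only if every drop-out is lost.

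That an article condenses a longer protocol is no answer here, because all three figures are printed and they do not agree.

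**Conclusion.** The point holds as a small inconsistency in the sample-size statement. On the stated figures, 15% drop-out from 110 per arm leaves 93.5 per arm (187 in total against 190), where dividing by 0.85 would call for 112 per arm. At 95 evaluable per arm, the target of 110 covers 13.6% drop-out.

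Power at 187 patients is about 79.6%. This assumes a true difference of 0, the margin, SD and alpha as stated, the normal approximation, and no contribution from any drop-out. To the extent that the planned model or imputation retains drop-outs, the loss is smaller.

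This is of the lowest severity. It concerns the accuracy of one sentence and should not be presented as the trial materially missing its 80% power. It takes the stated SD and margin as given and does not assess them.

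**What to change.** Keep 220 and correct the sentence in the Sample size section in one of two ways:

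- state that 110 per arm allows for about 13.6% drop-out with 95 per arm remaining; or
- keep 15% and state that about 187 evaluable patients would remain, with about 79.6% power on the stated inputs.

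In either case, show the allowance as n / (1 − drop-out) and state the assumed true difference of 0, if that is what was used.

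The cost is one sentence of wording. No further patients are needed, and the margin, the analyses and the decision rule stay as they are. The stated drop-out tolerance, or the stated power, becomes slightly less favourable.

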### Procedure

Randomization has been performed by a researcher unrelated to the study using a computer-generated sequence (Randomizer). In the program, the researcher generated 1 set of numbers with 220 numbers, which had a 1-to-2 range. Randomization is stratified according to the severity of the primary measures of depression (BDI-II) [23, 24] and anxiety (BAI) [25, 26], using the recommended cut-off in manuals. In the BDI-II, these are 0–13 for normal, 14–19 for mild, 20–28 for moderate, and for 29–63: severe depressive symptoms [24]. As for anxiety symptoms (BAI), cut-off are 0–7 for normal, 10–18 for mild, 16–25 for moderate, and 26–63 for severe [26]. Stratification is made to ensure a comparable proportion of severely depressed and anxious individuals in each group. For each subgroup (i.e., severe or less severe depression and/or anxiety), participants are randomly assigned to the UP or to TAU. In the UP condition, there are between 8 and 10 participants and 2 clinicians (therapist and co-therapist) per group. In the TAU condition, participants receive individual sessions with one therapist.

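### The single 220-number list described does not secure the stated severity stratification, and the strata and BAI bands are not cleanly defined

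*Protocol article*

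**What the plan says.** All of the allocation text is in the Procedure section of the protocol article.

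- **Mechanism.** A researcher outside the study used a computer program, and "the researcher generated 1 set of numbers with 220 numbers, which had a 1-to-2 range".
- **Stratification.** The same paragraph says randomization is stratified by severity on the BDI-II and the BAI, and gives the aim: "Stratification is made to ensure a comparable proportion of severely depressed and anxious individuals in each group".
- **Strata, first description.** Four bands per scale. For the BDI-II: "0–13 for normal, 14–19 for mild, 20–28 for moderate, and for 29–63: severe depressive symptoms". For the BAI: "cut-off are 0–7 for normal, 10–18 for mild, 16–25 for moderate, and 26–63 for severe".
- **Strata, second description.** "For each subgroup (i.e., severe or less severe depression and/or anxiety), participants are randomly assigned to the UP or to TAU".

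The Sample size section sets the recruitment target: "we decided to recruit 110 subjects in each group". The Analyses section takes as covariates only those demographic and clinical variables that baseline tests show to differ between arms. The section on treatment as usual adds the number of sessions. Neither names the stratification factors.

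**The concern.** Stratified allocation needs some device that works inside each stratum, such as a separate restricted list or minimisation. One list that runs through the whole trial, used in order of entry, takes no account of a patient's severity. The mechanism and the aim in the Procedure section therefore do not fit together.

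BDI-II and BAI scores are both the stratifiers and primary outcomes, so baseline severity is likely to be strongly prognostic. A chance imbalance in severity would then bear on the non-inferiority comparison, and under the Analyses section severity enters as a covariate only if a baseline test flags it.

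There is a second, separate fault. A reader cannot tell whether the strata are four bands per scale or two levels per scale, and the BAI bands as printed are neither exhaustive nor mutually exclusive.

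**Working it through.** **Inputs from the documents.** One list of 220 entries, each 1 or 2; target 110 per arm; margin 0.30, SD 0.83, one-sided alpha 0.05, power 80%, drop-out 15%; BDI-II bands 0–13, 14–19, 20–28, 29–63; BAI bands 0–7, 10–18, 16–25, 26–63.

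**Assumptions, not in the documents.** The share of severe patients is taken as 30% to 50%. Strata are taken as equal in size where a stratum size is needed.

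**1. The plan's own sample size.** n per arm = 2 × [0.83 × (1.645 + 0.842) / 0.30]² = 94.65, rounded up to 95. This agrees with the plan. The target of 110 matches 95 × 1.15 = 109.25, rounded up.

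**2. Arm totals if the list is unrestricted.** The size of one arm is Binomial(220, 0.5), with SD √220 / 2 = 7.4.

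| Event | Result |
|---|---|
| Exactly 110:110 | 5.4% |
| 100:120 or more uneven | 20% |
| Central 95% range for one arm | 95 to 125 |
| Smaller arm below 95 | 3.6% |

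**3. Cost of uneven totals in power.** Power = Φ[0.30 / (0.83 × √(1/n₁ + 1/n₂)) − 1.645].

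| Evaluable patients | 110:110 split | 95:125 split |
|---|---|---|
| All 220 | 85.0% | 84.4% |
| After 15% drop-out | 79.6% (93.5:93.5) | 78.9% (80.75:106.25) |

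The loss is 0.6 to 0.7 points, which is negligible.

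**4. Severity balance, unrestricted list.** Severe and less severe patients are each split by independent fair draws. The probability that the arms differ by 10 percentage points or more in share severe is 11% if 30% are severe, 13% if 40% are, and 16% if 50% are. With four equal strata (220 / 4 = 55), the 95% range for one arm within a stratum is 20 to 35. With sixteen equal strata (220 / 16, about 14), it is 3 to 11.

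**5. Severity balance if the list holds exactly 110 ones and 110 twos.** The number of severe patients in one arm is then hypergeometric. The SD of the difference in share severe is 2 × √[q(1 − q) / 219], where q is the share severe. This is 6.2 points at q = 0.3 and 6.8 points at q = 0.5. For the unrestricted list the approximate SD, √[q(1 − q) × 2 / 110], is 6.2 and 6.7 points. The chance of a difference of 10 points or more is 11% to 14%. Fixing the totals therefore does almost nothing for severity balance.

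**6. The bands.** Each score from 0 to 63 was checked against the printed bands. On the BDI-II every score falls in exactly one band. On the BAI, scores 8 and 9 fall in no band, and 16, 17 and 18 fall in both mild and moderate. All five scores lie below 26, the lower limit of the severe band.

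**The case against.** The strongest reply is that the article is condensed. It says patients are assigned within each subgroup, and block sizes and list mechanics are commonly left to the full protocol. It nowhere calls the list unrestricted, and a shuffled list of 110 ones and 110 twos fits the same words. This stands in part: simple randomisation is the natural reading but is an inference, so the range of 95 to 125 is conditional on it. It does not remove the conflict, because the one mechanism that is described does not serve strata even when its totals are fixed (step 5).

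A reader might infer more than the text supports:

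- **That 110:110 cannot occur.** It can. The list does not ensure it, and 110 per arm is stated as a recruitment target, not as a property of the list.
- **That power is compromised.** Uneven totals cost less than 1 point.
- **That the strata cannot be reconstructed for analysis.** With severe versus less severe subgroups they can, because every disputed BAI score is below 26 and the BDI-II bands are sound.
- **That allocation was not in fact stratified.** The article does not show this. It shows a description that does not fit the claim.

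It can also be said that residual imbalance is partly handled: arms are compared at baseline, differing variables become covariates, and baseline is a time level in the mixed model. That is fair, but it leaves adjustment for the design's own stratifiers to the outcome of a baseline test.

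**Conclusion.** The point holds as a conflict between the stated aim and the described mechanism, together with a definite error in the printed BAI bands.

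The list as described does not ensure comparable severity across arms. The chance of a gap of 10 points or more in share severe is about 11% to 16%, assuming that 30% to 50% of patients are severe and that the list is used without regard to stratum. If allocation was in fact made within strata by a restricted method, this risk does not arise and only the description needs correcting.

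The BAI gap (8 and 9) and overlap (16 to 18) are exact and need no assumption. They make stratum membership undefined only if all four bands are strata.

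**What to change.** 1. Define the strata once, as the subgroups the Procedure section already names: BDI-II 29 or more versus less, and BAI 26 or more versus less.
2. Correct the BAI bands so that they are exhaustive and do not overlap, after checking them against the manual that the article cites.
3. Report how allocation has actually been done: how many lists, any restriction, and how a patient's stratum determined the next assignment.
4. Pre-specify both severity factors as covariates in the primary mixed model, whatever the baseline tests show. Baseline is itself a level of time in that model, so state also whether the factors interact with time; a main effect alone shifts all visits equally and would do little to adjust the change from baseline.
5. Only if allocation so far came from the single list, use separate permuted-block lists with varying block sizes for the four strata for patients still to be recruited. The article gives January 2020 as the expected end of recruitment.

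The first four items are changes of text. The fifth needs a short amendment, a new list from the independent researcher, and coordination across the five centres. The total of 220 does not change.
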